### Covariates

Facility-level covariates include those that were found to be associated with pMTCT performance in analyses that are part of the wider research project that includes the SAIA intervention trial, including patient volume, staffing levels, availability of laboratory tests, geographic location (urban or rural), availability of community-based support groups, year of pMTCT initiation, and pMTCT approach (Option B+/B/A).

### Implementation process measures

Further qualitative data will be collected during the implementation process, and at the end of the trial, to facilitate the interpretation of the primary study results and increase the applicability of the SAIA intervention to other settings. The qualitative implementation process measures were designed based on the domains of the Consolidated Framework for Implementation Research (CFIR) [52], and intended to provide contextual information on factors that are important for the intervention’s acceptability, penetration and adoption by pMTCT staff and facility leadership, as well as factors impacting the quality, feasibility, and sustainability of the intervention’s application. Descriptive information will be collected on how the SAIA intervention was introduced, facility-level innovations that were proposed for testing, what was actually implemented, what went well and why, and what could be improved. Likert scale measures (scaled between 1 to 10) as well as open-ended questions will focus on manager and staff impressions on the acceptability of the intervention, utility of the intervention, leadership support, involvement of other agencies, intervention timing, staff capability to implement the intervention, clarity of roles to implement the intervention, ability of the intervention to meet staff and patient needs, and what the intervention fails to address.

### Data sources

#### Primary study outcomes

Health facility registries from ANC, maternities, and postpartum child care services are the source for monthly performance measures pre-, during and post-intervention at the 36 study facilities. Data extraction from registries is performed by two trained study team members in each facility, and compared for consistency. In cases of inconsistency, data collection procedures are redone, until monthly totals are in agreement. All project data are double-entered into a Microsoft Access^©^ database by each in-country study team and sent to the Seattle-based support staff for warehousing. Additional quality control procedures are carried out on a monthly basis on the centralized database to identify cases of missing data or outliers.

### Covariates

Additional facility-level descriptive factors will be collected via interviews with facility managers and direct observation by trained study personnel using a data collection instrument designed for the purposes of this study. Covariates cover information on the facility (size, geographic location, public/non-profit managed), staffing levels and structure, service utilization, available auxiliary services (laboratory, pharmacy, community outreach), and other similar factors that may affect both the adoption and effects of the intervention.

### Implementation process

In addition to the routinely reported administrative data, in-country study teams will collect descriptive implementation process data on an ongoing basis using data collection instruments designed for the purposes of this study. A 14-item questionnaire using Likert scales (ranging from 1 to 10) and open-ended questions was developed to gather data relevant to the CFIR domains, and will be applied weekly for the first four weeks of the SAIA intervention, followed by monthly for the remaining five months, with facility managers and a rotating group of facility nurses. This questionnaire will be complemented by field diaries maintained daily by study teams, and post-intervention key informant interviews with study assistants and in-country study managers.

### Analysis

The primary analysis approach to assess the impact of the SAIA intervention will rely on paired t-tests comparing the average outcome measures over the 12 months preceding the intervention, compared with the average over the three months directly following the intervention period, for the three study outcomes. As a secondary analysis approach, segmented regression analysis that controls for baseline outcome levels and trend to compare the monthly averages before versus after the intervention will be carried out for all three study outcomes. Change points will include a node at the beginning of the intervention period to reflect the introduction of the intervention; two additional terms will be added to the model at the end of the six-month intervention period to indicate the level change and trend change post intervention. To account for a three-month lag in the impact of the intervention, data from the first three months post initiation of the intervention will be excluded from analysis. Sub-analyses will be carried stratified by country and facility size to assess subgroup effects.

Because facilities will be randomly selected and allocated to intervention and control facilities, we do not expect to perform adjusted analyses. However, descriptive characteristics will be compared between intervention and comparison facilities using student’s *t*-test and chi-square tests to assess potential imbalance between study arms, and subsequent analyses will consider covariates significant in bivariate analysis for inclusion in the final model in a stepwise fashion. In addition, because outcomes are reported as a monthly summary measure at the facility level, no additional procedures will be implemented to control for potential intra-class correlation at the cluster (health facility) level. Autocorrelation will be assessed using the Durbin-Watson statistic, and adjusted for if appropriate.

Descriptive analyses will include visual inspection of data for time trends across the study facilities, as well as within each facility, to identify trends, assess whether specific workflow adaptations led to improvements in the pMTCT cascade, and describe the sustainability of effects associated with individual adaptations. Those adaptations that are found to have dramatic or sustained effects will be documented as part of identifying best practices for pMTCT improvement. Exploratory bivariate analyses using student’s t-tests and chi-square tests will be carried out among facilities that showed large improvements in study outcomes during the six-month implementation period to identify descriptive factors that may be associated with adoption or may mediate the impact of the SAIA intervention.

Analysis of the implementation process data will include aggregate reporting of individual items from the Likert scales, as well as disaggregated analysis by study country, and by facilities found to have relatively better success with the intervention. The constant comparison method will be used to describe responses to qualitative data from open-ended questions, field diaries, and key informant interviews.

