### Goals and objectives

The goal of this study is to strengthen pMTCT programs in the three study countries by applying and evaluating systems analysis and improvement approaches, to build on existing experience with these techniques.

Our primary hypothesis is that identifying modifiable barriers to completing steps in the pMTCT cascade and applying locally-defined innovations will lead to measurable improvements in the performance of pMTCT services over and above those observed during the same time period in control facilities. The primary outcomes for this pragmatic trial focus on the proportion of women and children pairs successfully progressing through the pMTCT cascade from HIV screening at first antenatal care (ANC) visit, to successful receipt of antiretroviral medicines, and ending with HIV screening in infants. These measures are sensitive to the systems analysis and improvement (SAIA) intervention, readily measurable, and represent steps that are essential for successful prevention of HIV acquisition in children. Additional qualitative data collection embedded into the trial is designed to describe intervention characteristics that may influence the success of the SAIA intervention, the implementation environment, and the implementation process.

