### Trial design

This study employs a two-arm, 1:1 cluster randomized trial design to assess the effectiveness of the SAIA intervention. The unit of intervention is the health facility. A total of 36 health facilities are part of the trial, including 18 intervention and 18 comparison facilities (six intervention and six comparison facilities per country).

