### Sample size

Sample size estimates are based on the health facility as the unit of analysis, and were calculated to detect the change in the proportion of HIV-infected pregnant women receiving antiretroviral medicines in pregnancy (arguably the most important endpoint of the study). Using program data from 2009 to 2010, we estimated a mean pre-intervention baseline of 50%, and predicted a mean post-intervention level of 70% for intervention facilities (mean change score = 20%) and 50% for control facilities (mean change score = 0%), and a standard deviation of yearly change scores of 11%. Assuming α = 0.05 and β = 0.80, the sample size is sufficient to detect an 11% and a 20% difference in mean change scores across the three countries and at the country level, respectively (Table 4).

**Table 4 T4:** Sample size and detectable change in study outcomes

**Sample size (Intervention: Control)**	**Detectable alternative in gain scores across intervention and control facilities**
6:6	19.7%
12:12	13.2%
18:18	10.6%

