### Trial status

Implementation of the SAIA intervention began in January 2014 in all study countries, and is being sequentially introduced in the 18 intervention facilities (six in each study country). At the time of submission, the intervention has been introduced in nine facilities (four in Côte d’Ivoire, two in Kenya, and three in Mozambique).

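### The primary analysis is worded as a before/after paired t-test with no between-arm contrast, which contradicts the trial's hypothesis and the test it was sized for

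*Protocol article*

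**What the plan says.** All references are to the protocol article.

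- **Trial design** describes a "two-arm, 1:1 cluster randomized trial design to assess the effectiveness of the SAIA intervention", with 18 intervention and 18 comparison facilities.
- **Goals and objectives** states the primary hypothesis as improvement "over and above those observed during the same time period in control facilities".
- **Sample size** works with facility change scores: a mean change of 20 points with the intervention, 0 in controls, SD 11. It calls the sample "sufficient to detect an 11% and a 20% difference in mean change scores", overall and within a country respectively. Table 4 gives the detectable alternative in gain scores across the two arms as 19.7% (6:6), 13.2% (12:12) and 10.6% (18:18).
- **Analysis** states that the primary approach will "rely on paired t-tests comparing the average outcome measures over the 12 months preceding the intervention". The other side of that comparison is the mean of the first three months once the intervention has ended, and the test is applied to each outcome.
- **Analysis**, secondary approach: "segmented regression analysis that controls for baseline outcome levels and trend to compare the monthly averages before versus after the intervention". The terms listed are a node at the start of the intervention and level and trend changes at its end.
- The only comparison of arms named in that section is of descriptive characteristics, to look for imbalance.

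**The concern.** A paired t-test of pre against post means asks whether facilities changed. The hypothesis asks whether intervention facilities changed more than controls did. Only the second question uses the randomisation. Nor can the pairing be read as arm-to-arm matching: under Randomization, three of six facilities in each country-by-volume group are drawn at random, so there are no matched pairs and each facility can be paired only with itself.

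The secondary model does not supply the missing contrast, because none of its listed terms involves arm.

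The distinction matters because outcomes may move in both arms without any SAIA effect. The Discussion reports that pMTCT guidelines were shifting quickly towards combination therapy for all HIV-infected pregnant women. That bears directly on the second outcome, which is the one used for sizing. A before/after test cannot separate such a change from the intervention. Leaving the analysis text and the sizing text in conflict also leaves the choice of primary test open after the data are seen.

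**Working it through.** **Inputs.** From Sample size: SD of change scores 11 points; alpha 0.05; the printed β of 0.80 is read as power 0.80, since only that reading gives the table. From Table 4: facilities per arm n = 6, 12, 18. Alpha is taken as two-sided, because the one-sided version gives 16.98, 11.53 and 9.30 and does not match.

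**Step 1: reproduce Table 4 as a between-arm test.** For a two-sample t-test on change scores, the standard error is SE = 11 × √(2/n), the degrees of freedom are 2n − 2, and power is P(T > t_crit), with T noncentral t and noncentrality d/SE.

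| n per arm | SE | t_crit | Printed d | d/SE | Power at printed d | d for 80% power |
|---|---|---|---|---|---|---|
| 6 | 6.35 | 2.228 | 19.7 | 3.10 | 0.798 | 19.75 |
| 12 | 4.49 | 2.074 | 13.2 | 2.94 | 0.802 | 13.16 |
| 18 | 3.67 | 2.032 | 10.6 | 2.89 | 0.802 | 10.57 |

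All three rows agree with the table to rounding.

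**Step 2: try the test named in Analysis.** For a paired t-test on m facilities, SE = 11/√m and the degrees of freedom are m − 1.

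| Table 4 row | Printed | Paired, one arm (m = n) | Paired, both arms pooled (m = 2n) |
|---|---|---|---|
| 6:6 | 19.7 | 15.78 | 9.78 |
| 12:12 | 13.2 | 9.78 | 6.57 |
| 18:18 | 10.6 | 7.71 | 5.28 |

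No row matches. The trial was sized for the two-sample test, not the one named as primary.

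**Step 3: what the literal test would do.** Suppose SAIA has no effect and both arms share a secular change s. The documents give no value for s, so the range is assumed. Facility changes are taken as independent with SD 11. For the 18 intervention facilities, SE = 11/√18 = 2.59, t_crit on 17 df = 2.110, and noncentrality = s/2.59.

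| s (points) | s/SE | P(paired test rejects) | P(two-sample test rejects), simulated |
|---|---|---|---|
| 0 | 0 | 0.05 | 0.051 |
| 2.5 | 0.96 | 0.15 | 0.050 |
| 5 | 1.93 | 0.44 | 0.050 |
| 10 | 3.86 | 0.95 | 0.050 |

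The two-sample test holds its level because the shared change cancels.

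**Step 4: would separate paired tests by arm help?** Reading significance in the intervention arm and none in the control arm as an effect gives a false positive in about 0.25 of simulated trials at s = 5 and 0.17 at s = 7.5. It is not a substitute for a direct comparison.

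**The case against.** The best defence is that this is loose wording. Analysis does not confine the paired tests to intervention facilities. Its next paragraph relies on random allocation to justify an unadjusted analysis and checks balance between arms, which makes sense only if the arms are to be compared. Study measures collects all 21 months in both arms, and Sample size is built on gain scores by arm. The reproduction of Table 4 as a two-sample test is itself evidence that a between-arm comparison was intended. This stands, and it rules out a stronger reading: a reader might infer that the trial discards its randomised control or will certainly report secular change as a SAIA effect. The documents do not support that. They show a primary test stated wrongly against their own hypothesis and sizing.

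The rejection rates are also conditional. They need the test to be run on the 18 intervention facilities alone and a secular change whose size is nowhere given.

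A second tempting inference comes from the staggered start, since the intervention "is being sequentially introduced in the 18 intervention facilities (six in each study country"): that unaligned calendar windows would bias the comparison by some number of points. This does not follow. Every facility has the same 12-month, 6-month and 3-month structure, so the pre and post midpoints are 6 + 6 + 1.5 = 13.5 months apart whatever the start date. Under a linear trend, shifting the whole window changes nothing. How comparison facilities receive their dates is detail that an article may leave to the full protocol.

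It can be said too that model terms for a secondary analysis belong in the analysis plan. That has some force, and the segmented regression matters here mainly because, as described, it does not supply the contrast the primary test lacks. Condensation does not excuse the primary test itself: the article names a specific test, and it is the wrong one.

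**Conclusion.** The primary analysis is wrong as written and must be corrected. It contains no between-arm contrast, whereas the hypothesis and Table 4 both concern a difference between arms. That conflict, and the mismatch with Table 4, rest only on figures in the article, with two-sided alpha and power 0.80 as the readings that reproduce the table.

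The size of the consequence rests on assumptions: a literal paired test in the 18 intervention facilities, SD 11, independent facility changes and a shared secular change of unknown size. Over the assumed range of 0 to 10 points, the false-positive probability runs from the nominal 0.05 to 0.95. The reported guideline changes make a non-zero shift plausible but do not quantify it.

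**What to change.** 1. State the primary test as a between-arm comparison of each facility's change, defined as the 3-month post mean minus the 12-month pre mean. Use either a two-sample t-test on the change scores or an ANCOVA of the post mean on the baseline mean. Either should respect the country and volume strata used in randomisation.
2. Add arm-by-level-change and arm-by-trend-change terms to the segmented regression and name them as its effect estimates.

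The cost is analysis wording only. Comparison-facility data are already planned for all 21 months, and no facilities are added. The two-sample test keeps the 10.6-point detectable difference (10.57 computed), and power for the planned 20-point difference exceeds 0.99. Fitting the six strata (three countries by two volume groups) takes the residual degrees of freedom from 34 to 29. With SD held at 11, that moves the detectable difference only to 10.63, still 10.6 to the printed precision.

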### Study timeline

The total data collection and implementation period is designed to cover 21 months, which includes 12 months of pre-intervention data collection, six months of intervention implementation, and three months of post-intervention data collection. The 12-month timeframe for pre-intervention data collection was chosen to generate stable baseline study outcomes despite monthly temporal fluctuations in these measures. A total of six months was selected for implementing the study intervention to provide sufficient time for the intervention to be adopted and lead to improvements, to allow for a sufficient number of iterative system analysis and improvement cycles to lead to sustainable performance improvements (assuming that each cycle will last on average four to six weeks, this timeframe will allow for between four and six cycles per facility), and to be feasible to complete within the specified funding timeline.

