### Study measures

#### Primary study outcomes

The three study outcomes include the proportion of women screened for HIV during their first ANC visit; the proportion of HIV infected women receiving antiretroviral medications during pregnancy (either bi-prophylaxis using AZT or combination antiretroviral therapy); and the proportion of infants born to HIV-infected women screened for HIV at six weeks postpartum (or two months in the case of Côte d’Ivoire, following national norms) (Table 3). These outcome measures were selected because they reflect successful progression through steps in the pMTCT cascade, they are likely sensitive to system-level improvements, and they represent steps that, if changed, would meaningfully alter patterns of HIV transmission or access to maternal and infant HIV care. Furthermore, these measures reflect national pMTCT protocols, and are therefore well understood and available in all three study countries. Data will be collected over 12 months before the intervention, during the six-month intervention, and three months after the intervention in both intervention and comparison facilities (21 time points and 36 measurements per time point).

**Table 3 T3:** pMTCT outcome measures

**Study measure**	**Numerator/Denominator**
1. Uptake of HIV counseling and testing	$\frac{\#\mathrm{women}\;\mathrm{counseled}\;\mathrm{and}\;\mathrm{tested}\;\mathrm{for}\;\mathrm{HIV}\;\mathrm{in}\;\mathrm{their}\;\mathrm{first}\;\mathrm{ANC}\;\mathrm{visit}}{\#\mathrm{first}\;\mathrm{ANC}\;\mathrm{visits}}$
2. Use of appropriate ARVs in pregnancy for prophylaxis or initiation of cART	$\frac{\#\mathrm{HIV}‒\mathrm{infected}\;\mathrm{pregnant}\;\mathrm{women}\;\mathrm{starting}\;\mathrm{AZT}\;\mathrm{prophylaxis}\;\mathrm{or}\;\mathrm{cART}}{\#\mathrm{women}\;\mathrm{testing}\;\mathrm{HIV}‒\mathrm{positive}\;\mathrm{in}\;\mathrm{ANC}\;3\;\mathrm{months}\;\mathrm{previously}}$
3. Infant HIV determination	$\frac{\#\mathrm{infants}<6\;\mathrm{weeks}\;\mathrm{of}\;\mathrm{age}\;\mathrm{receiving}\;a\;\mathrm{PCR}\;\mathrm{test}}{\#\mathrm{women}\;\mathrm{testing}\;\mathrm{HIV}‒\mathrm{positive}\;\mathrm{in}\;\mathrm{ANC}\;5\;\mathrm{months}\;\mathrm{previously}}$

ANC: Antenatal care; ARV: Antiretroviral; AZT: Azidothymidine; cART: combination antiretroviral therapy; HIV: Human immunodeficiency virus; PCR: Polymerase chain reaction.

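### The segmented regression dates its first change point at the start of SAIA but deletes the next three months, so a start-of-SAIA coefficient is extrapolated and can be biased or badly imprecise

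*Protocol article*

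**What the plan says.** The Study timeline section of the Protocol article sets out "12 months of pre-intervention data collection, six months of intervention implementation, and three months of post-intervention data collection", which the Primary study outcomes section counts as "21 time points and 36 measurements per time point".

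The Analysis section gives the regression a secondary role, with SAIA as the dividing event: "As a secondary analysis approach, segmented regression analysis that controls for baseline outcome levels and trend to compare the monthly averages before versus after the".

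It then fixes three things in one paragraph:

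- First change point: "Change points will include a node at the beginning of the intervention period to reflect the introduction of the intervention".
- Second change point, placed where SAIA finishes: "two additional terms will be added to the model at the end of the six-month intervention period to indicate the level change and trend change".
- Exclusion: "data from the first three months post initiation of the intervention will be excluded from analysis". The reason offered is a delay before any effect shows: "To account for a three-month lag in the impact of the intervention".

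Nothing moves the first change point, or the time variable that runs from it, to the end of the excluded window. The primary analysis is separate and looks at the months once SAIA is over: "paired t-tests comparing the average outcome measures over the 12 months preceding the intervention, compared with the average over the three months directly following".

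**The concern.** The lag sentence and the node sentence pull against each other. The first says that impact is not expected to show for three months, and removes those months. The second dates the effect at the start of those same months. The retained intervention segment is three points (months 16, 17 and 18), lying 3.5 to 5.5 months after the node.

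If the node carries a level and a slope, the level is read off a line extended back over the gap. If it carries only a slope, the fitted line has to climb through months in which the plan expects nothing to happen. The slope-only reading is plausible, because the end of SAIA is given explicit level and trend terms while the start is given only a node.

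At stake is the coefficient that readers will take as the effect of introducing SAIA, for all three outcomes. This is also the only planned between-period analysis that uses the baseline trend and the intervention months.

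**Working it through.** **Inputs from the Protocol article.** Periods of 12 + 6 + 3 = 21 months (Study timeline). Removing months 13 to 15 leaves 18: months 1-12, 16-18 and 19-21. Baseline 50%, with a gain of 20 points under SAIA and 0 in controls (Sample size). The plan gives no figure for this regression. Its only design calculation, Table 4, reproduces: (t0.975 + t0.80) × 11 × √(2/18) = 10.58 against the printed 10.6. The point does not depend on it.

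**Assumptions, not in the document.** Flat baseline and flat control series, independent errors with residual SD σ, and two effect shapes that respect the stated lag:

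- Ramp: 6.67, 13.33 and 20 points at months 16, 17 and 18, then 20.
- Step: 20 points from month 16 onward.

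**Model.** Ordinary least squares on the 18 retained months:

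y = b0 + b1·t + L1·[t>k] + S1·(t-k)·[t>k] + L2·[t>18.5] + S2·(t-18.5)·[t>18.5]

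Here k = 12.5 is the start of SAIA and k = 15.5 is the end of the excluded window. L1 or S1 is omitted for the slope-only or level-only node.

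**Level + slope, ramp.** Each segment is its own line. The slope over months 16-18 is (20 - 6.67)/2 = 6.67 per month. Read back to the node:

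- k = 12.5: 6.67 - 3.5 × 6.67 = -16.67.
- k = 15.5: 6.67 - 0.5 × 6.67 = +3.33.

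**Precision of that level.** Var(L1)/σ² = 1/3 + (17-k)²/2 + 1/12 + (k-6.5)²/143.

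- k = 12.5: 0.333 + 10.125 + 0.083 + 0.252 = 10.793, so SE = 3.29σ.
- k = 15.5: 0.333 + 1.125 + 0.083 + 0.566 = 2.108, so SE = 1.45σ.
- Effect at month 17, same formula with k = 17: 0.333 + 0 + 0.083 + 0.771 = 1.188, so SE = 1.09σ.

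Like for like, the start level is 3.29/1.45 = 2.3 times less precise.

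**All combinations** (points; slopes per month; last column is the mean fitted effect in months 19-21, true value 20):

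| Start terms | Shape | k | L1 | S1 | L2 | S2 | Months 19-21 |
|---|---|---|---|---|---|---|---|
| level + slope | ramp | 12.5 | -16.67 | 6.67 | -3.33 | -6.67 | 20.0 |
| level + slope | ramp | 15.5 | 3.33 | 6.67 | -3.33 | -6.67 | 20.0 |
| level + slope | step | either | 20 | 0 | 0 | 0 | 20.0 |
| slope only | step | 12.5 | - | 4.09 | -5.64 | -4.17 | 18.8 |
| slope only | step | 15.5 | - | 6.52 | -7.51 | -7.12 | 11.2 |
| slope only | ramp | 12.5 | - | 3.26 | 1.36 | -3.19 | 21.0 |
| level only | step | either | 20 | - | 0 | 0 | 20.0 |
| level only | ramp | either | 12.37 | - | 6.53 | -0.09 | 18.8 |

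In the slope-only step row at k = 12.5, the line overshoots to 24.5 points at month 18.5. The model then reports a drop of 5.64 points and a falling trend, although the gain is fully kept. Moving that slope-only node to 15.5 makes the fit worse: the residual sum of squares rises from 37 to 190.

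**Sensitivity to coding.** With nodes coded at months 12, 15 and 18 instead of half-months, the ramp start level is -20 at month 12 and 0 at month 15, with SE 3.62σ and 1.71σ. The slope-only false loss under the step is then 3.3 points and 3.8 points per month.

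**The case against.** The strongest reply is that much of this is parametrisation. With level and slope terms, moving the node changes no fitted value, no intervention slope and no end-of-SAIA term; only the number called the start level differs. With a level term alone, once months 13-15 are gone, an indicator starting at 12.5 and one starting at 15.5 are the same column. Level + slope also recovers a delayed step exactly. All of this is correct.

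A second reply is that the exclusion may handle a transition phase, not a period of no effect. Step four of the intervention looks for quick gains two to six weeks after each change. If the gain rose linearly from the start of SAIA to 20 points at month 18, a slope at the start node would be right (20/5.5 = 3.64 per month). That also stands as arithmetic, but such a rise does not fit the paragraph's own three-month lag.

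A third reply is that the node's exact terms belong in a fuller document. Agreed, and their absence is not the point. The date of the node and the reason for the exclusion are both stated, and they conflict.

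A reader might infer that the start-of-SAIA effect must come out wrong, or that the regression would contradict the primary result. The document does not support either. The bias needs particular pairings of terms and effect shape. With the node at the start of SAIA, the fitted effect in months 19-21 stays between 18.8 and 21.0 against a true 20 for both shapes, and the primary t-tests use neither the node nor months 13-18.

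**Conclusion.** The point holds in a limited form. The node date conflicts with the stated lag, so a start-of-SAIA coefficient rests on months 16-18 projected back over three empty months. With level and slope terms its SE is 3.29σ instead of 1.45σ, whatever the effect shape. Its value is about -17 points if the gain builds after the lag (-20 with whole-month coding). With a slope-only node and a sustained step, the harm reaches the end-of-SAIA terms as a false loss of about 5.6 points (3.3 with whole-month coding). A level-only node does not depend on the date.

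These sizes rest on the assumed shapes, a flat baseline and independent errors, scaled to the planned 20 points. Deleting a lag period is not itself a fault. The reach is one secondary analysis, so this is worth correcting but does not threaten the primary comparison.

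**What to change.** Keep months 13-15 excluded. State that the first change point, and the clock for time since the change, sit at the end of the excluded window (start of study month 16). Include a level term there, and centre any slope within months 16-18. Centred at month 17, the level term is the average fitted effect over those three months: 13.3 points under the ramp and 20 under the step, with SE 1.09σ. Do not move a slope-only node without adding the level term. Report the between-arm fitted effect over the observed months instead of a coefficient at the start of SAIA.

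The cost is one or two sentences and a recoded time variable, with no new data. A separate estimate of an immediate effect is given up, but the deleted months could not have supported it.
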